#### Quality of surgery

Surgeons who participate in the study are required to follow the TME surgical principles (leave sharp scoring under direct vision in the presacral space; keep the pelvic visceral fascia intact; resect the whole mesorectum or make sure that the distal mesorectum of the tumor is not <5 cm and the extent of intestinal resection is ≥2 cm from the distal tumor) to complete radical rectal cancer resection. The following photos will be acquired during the operation to upload to the data system: IMV after free ligation (undissected IMV), after the third station lymphadenectomy, and *in vitro* specimen (including the intestinal tube and mesangium, with ruler or reference placed next to the specimen). In the HL group, 253 lymph nodes and IMV root lymph nodes will be dissected separately and sent for regular pathological examination, and, in the LL group, 253 lymph nodes will be dissected separately and sent for routine pathological examination. Surgeons need to evaluate the quality of the excised *in vitro* specimens. Referring to the concept of the quality grading of rectal cancer gross specimens proposed by Nagtegaal *et al.* [14], the criteria are as follows: (i) high-quality: mesorectal plane resection, intact mesorectum, no defect of >5 mm on the fascia surface of the pelvic visceral layer, no exposed muscularis of the intestinal wall, and a cylindrical appearance; (ii) moderate-quality: mesorectal internal plane resection, intact mesorectal, pelvic visceral fascia surface defect of >5 mm, no muscularis of the intestinal wall, sufficient mesorectal margins, and an approximately conical appearance; (iii) low-quality: myometrial propria plane resection, incomplete mesorectum, pelvic visceral fascia with a defect of >5 mm, and muscularis of the intestinal wall visible and conical in appearance.

The expert review committee (research initiator: the person in charge of the First Medical Center of the Chinese People’s Liberation Army General Hospital; participating members: the person in charge of Peking Union Medical College Hospital and the person in charge of Peking University Cancer Hospital) randomly select the research cases; after discussion, no fewer than two-thirds of the experts determine that the surgical quality meets the research requirements and the cases are qualified to be enrolled. If they do not meet the requirements of the enrolled surgical quality, they are excluded.

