### Subject management

#### Subject exclusion criteria

After being selected for randomization, the patient requested to withdraw from the study because of various considerations.There are no data after entering the queue.Intraoperative findings of tumor involvement requiring multivisceral resection, distant metastasis, or inability to complete the planned laparoscopic radical resection.Other reasons need to be excluded as determined by the investigator.

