##### Dropout treatment

When subjects drop out, the investigator will contact the subjects as much as possible by visiting their homes, making appointments for follow-up, telephone, and letters, among others, asking for reasons and to complete the evaluation items that can be completed. If the experimental case is withdrawn because of adverse reactions, the investigator should take corresponding treatment measures according to the actual situation of the subject. The relevant test data of the expulsion cases are properly maintained, i.e. they are kept as documents, and they are also required for the full analysis set (FAS) statistics. Patients who have dropped out do not need to be replaced.

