### Statistical methods

#### Evaluation and analysis of efficacy

FAS population: This dataset is derived from the minimal and reasonable culling of subjects from all randomized subjects, as close as possible to the population of subjects that conform to the principles of the intention-to-treat (ITT) analysis. ITT: A patient is considered an ineligible study subject and is placed in the ITT population as a result of a change in the assigned surgical regimen or the implementation of an unplanned alternative treatment on the basis of the judgment of the study group or the patient’s special condition. ITT analysis of the primary and secondary endpoints will be performed by using whole-population data.

Eligible for the protocol (PP) population: Subjects in the FAS who meet the following conditions—the baseline value of the main indicators is complete, meets the inclusion criteria and does not meet the exclusion criteria, completes the specified treatment regimen after random assignment according to the clinical trial protocol, and has good compliance. For auxiliary purposes, if the difference between the ITT and PP analysis groups is >10%, then the ITT analysis is used.

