#### Enrollment

All the enrolled patients should be screened in strict accordance with the inclusion criteria and the qualified research centers can conduct intraoperative randomization after intraoperative exploration and definitive radical surgical resection to minimize the rejection rate of the enrolled patients.

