#### Postoperative follow-up

Researchers at each research center can establish stable contact with subjects (such as by establishing a WeChat follow-up group) to facilitate follow-up tracking. The research center needs to complete the follow-up and upload the follow-up data in a timely manner according to the follow-up time node, which needs to be completed within 60 days before and after the follow-up time node in the first year of follow-up and within 90 days before and after the follow-up time node in the second and third years of follow-up. For enrolled patients whose follow-up time exceeds the follow-up time window, the expert review committee and statistical experts will discuss and determine the analysis data set to be included in the enrolled cases.

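### Post-allocation exclusion rules conflict with the promised intention-to-treat analysis, so the protocol permits a primary DFS comparison that is not of the randomised groups

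*Protocol article*

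**What the plan says.** **Rules that keep patients in.** Evaluation and analysis of efficacy states that primary and secondary endpoints will be analysed by ITT on the whole population. It places patients whose assigned operation was changed in the ITT population. Dropout treatment says of the records of dropped-out cases that "they are also required for the full analysis set (FAS) statistics".

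**Rules that take patients out.**
- Quality of surgery: an expert committee reviews randomly selected cases, and at least two-thirds of its members must find the quality acceptable. For those that fail: "If they do not meet the requirements of the enrolled surgical quality, they are excluded".
- Subject exclusion criteria, under Subject management and separate from the eligibility criteria: "After being selected for randomization, the patient requested to withdraw from the study because of various considerations"; patients with no data after entry; "Intraoperative findings of tumor involvement requiring multivisceral resection, distant metastasis, or inability to complete the planned laparoscopic radical resection"; and "Other reasons need to be excluded as determined by the investigator".

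**Rules that leave the set open.**
- Postoperative follow-up, under Quality-control measures: for patients outside the visit window, "the expert review committee and statistical experts will discuss and determine the analysis data set".
- Evaluation and analysis of efficacy: the full analysis set may drop a limited number of randomised patients. For the PP set, described as auxiliary, "if the difference between the ITT and PP analysis groups is >10%, then the ITT analysis is used".

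**Timing.** Enrollment, under Quality-control measures, specifies "intraoperative randomization after intraoperative exploration and definitive radical surgical resection".

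**The concern.** Randomisation happens during the operation. Specimen quality, failure to complete the operation, withdrawal and the investigator's later judgement therefore all arise after allocation, and each can depend on which operation was allocated. The high-ligation arm adds mobilisation of the vein up to the pancreas and dissection of the root nodes. Such patients may also have a worse prognosis than the rest of their arm. If they leave the primary analysis unequally, the DFS difference partly reflects who was removed, and it can favour either arm.

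The people deciding are not shown to be shielded from allocation. The Blinding section says surgeons cannot be blinded. It names imaging assessors, pathologists and data analysts as blinded, but does not mention the quality committee. Because that committee reviews only a random selection of cases, equally poor operations stay or go according to whether they were picked.

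If the conflict is left until outcomes are known, the choice of primary set could be driven by the data.

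**Working it through.** **1. Passages side by side.**

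| Event after allocation | Rule that removes or leaves open | Rule that keeps |
|---|---|---|
| Fails quality review | Quality of surgery: excluded | Efficacy section: ITT on the whole population |
| Withdraws | Subject exclusion criteria: excluded | Dropout treatment: needed for the full analysis set |
| Planned operation not completed | Subject exclusion criteria: excluded | Efficacy section: changed operation stays in ITT |
| Investigator's other reasons | Subject exclusion criteria: excluded | Efficacy section: ITT on the whole population |
| Visit outside window | Quality-control follow-up: set decided case by case | Efficacy section: ITT on the whole population |
| ITT and PP differ by 10% or less | No rule given | Efficacy section: ITT on the whole population |

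No sentence ranks one column above the other.

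**2. Benchmark from the plan.** Number of research cases assumes 3-year DFS of 85% and 78%, a 7-point difference, with 758 per arm. Under exponential survival the hazard ratio is ln(0.85)/ln(0.78) = 0.654. Against the stated margin of 0.90, reading the printed β = 0.8 as 80% power, events = 4(1.960 + 0.842)² / [ln(0.654/0.90)]² ≈ 308. With 2 years' uniform accrual, 3 years' further follow-up and 20% loss over 3 years, this needs 746 per arm, within 2% of 758. The sample size is not in dispute here.

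**3. Size of a selective exclusion (assumed values).** Let an arm have true 3-year DFS of 0.78, and let a fraction f with DFS of 0.60 be excluded. The documents give neither f nor 0.60. Retained DFS = (0.78 − 0.60f)/(1 − f).

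- f = 0.05: (0.78 − 0.03)/0.95 = 0.789, a shift of 0.9 points (0.95 before rounding).
- f = 0.10: (0.78 − 0.06)/0.90 = 0.800, a shift of 2.0 points, or 2.0/7 = 29% of the design difference.
- f = 0.06 in one arm and 0.04 in the other: 0.744/0.94 = 0.7915 and 0.756/0.96 = 0.7875, a difference of about 0.4 points.

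**4. Effect on type I error.** Take both arms truly at 78% with 758 per arm, exclusions in one arm only, and a normal approximation for the difference in 3-year proportions without censoring. The two-sided error, nominally 0.05, becomes about 0.07 at f = 0.05 and 0.15 at f = 0.10. If the excluded patients had 50% DFS instead of 60%, the shifts would be 1.5 and 3.1 points and the errors about 0.11 and 0.31.

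**5. Exclusion unrelated to arm or outcome.** Only power is lost. Power = Φ(2.802√(1 − f) − 1.960), which falls from 0.80 to 0.78 at f = 0.05 and 0.76 at f = 0.10.

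**The case against.** The strongest reply is that the protocol already commits to ITT on the whole population and keeps dropouts, so the exclusion lists could be read as PP criteria only. That stands in part. A reader might infer that ITT has been abandoned, and the documents do not say so. But neither exclusion list is tied to the PP set, and the quality section treats passing review as the condition for counting as enrolled. The conflict therefore remains.

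Other stronger readings also go too far:
- **PP replaces ITT.** The 10% rule only implies this. PP is called auxiliary, and the only stated consequence is that ITT is used. What the text shows is a gap at 10% or less.
- **A late visit removes a patient.** The text gives a case-by-case choice of data set, not removal.
- **The committee sees the allocation.** Photographs of the ligated vein are uploaded, but the text does not say what the committee reviews or whether it is blinded.
- **High ligation takes longer and so produces more exclusions.** The Introduction and Discussion report similar operation times. A more extensive dissection is supported; a longer one is not.

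It is also fair to say that the specimen grades concern the mesorectal plane and that the main surgical steps are shared by both arms. Strongly arm-dependent exclusion is therefore possible but not shown. The one-arm figures are upper illustrations, since the same rules apply to both arms. Finally, if randomisation follows exploration, the metastasis criterion is mostly redundant rather than a source of bias.

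**Conclusion.** The point holds as an unresolved contradiction about the primary analysis population. Followed as written, the quality and subject exclusion rules would take randomised patients out of the DFS comparison on post-allocation grounds, while the efficacy and dropout sections say they stay. The protocol therefore permits a non-randomised comparison; it does not prescribe one.

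The size cannot be derived from the documents. On the assumed 60% DFS among those excluded, it runs from about 0.4 points (6% versus 4% excluded) to 0.9–2.0 points (5–10% of one arm only). Confidence is high in the conflict and low in any particular magnitude. Because the primary endpoint is affected and the remedy is wording, it should be settled before outcomes are known.

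**What to change.** - **Primary set.** State that the primary analysis includes every randomised patient in the allocated arm, whatever the surgical quality, conversion, withdrawal from visits or visit timing. Use a withdrawn patient's data up to the last assessment, unless consent for their use is withdrawn.
- **Missing data.** Estimation of missing values for major indicators uses complete cases below 10% missing. Align it so that patients censored for DFS are not dropped as incomplete.
- **Exclusions.** Confine the Subject exclusion criteria, the committee's quality exclusions and the out-of-window decisions to the PP or sensitivity sets.
- **10% rule.** Delete it. ITT is always primary and PP supportive.
- **Randomisation time.** Reconcile Subject exclusion criteria with Enrollment under Quality-control measures. Randomise after exploration and before the inferior mesenteric vein is ligated, so that metastasis or unresectability found at exploration is a screen failure before randomisation.

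**Cost:** protocol wording only, with no extra data. Some poor-quality or uncompleted operations stay in the primary analysis and may dilute the effect slightly; the PP analysis can show by how much.

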#### Postoperative follow-up

Researchers at each research center can establish stable contact with subjects (such as by establishing a WeChat follow-up group) to facilitate follow-up tracking. The research center needs to complete the follow-up and upload the follow-up data in a timely manner according to the follow-up time node, which needs to be completed within 60 days before and after the follow-up time node in the first year of follow-up and within 90 days before and after the follow-up time node in the second and third years of follow-up. For enrolled patients whose follow-up time exceeds the follow-up time window, the expert review committee and statistical experts will discuss and determine the analysis data set to be included in the enrolled cases.

#### Data quality

Each center has one research assistant and one follow-up officer (responsible for data entry and follow-up in the center). The data-entry system can carry out online quality control of the data in real time and the research assistants of each center are responsible for the supervision and quality control of the research data of the center, identification and correction of the problems in the data-entry process in a timely manner, coordination of the research progress, and facilitation of follow-up completion in a timely and effective manner. The follow-up staff of each center will hold a summary meeting every 6 months to analyse the reasons for dropout, discontinuation, and lack of research, and they will correct the deviations. The person in charge of each center will hold a summary meeting once a year. The data of all the enrolled patients will be maintained or copied and backed up and reviewed by the person in charge of each center at the annual summary meeting to ensure that each enrolled patient meets predetermined research procedures.

## Discussion

The complex anatomy of the IMV (receiving venous branches from the sigmoid colon, descending colon, and splenic flexure and typically accompanying the IMA) and its variable lymphatic drainage patterns underlie the ongoing debate regarding the optimal ligation level [15]. Japanese scholars believe that rectal lymphatic drainage is distributed upward along the artery to the root of the IMA [11]. European and American scholars have studied rectal lymphatic drainage by using mercury in cadavers and it is generally believed that rectal lymph drains upward along the artery to the root of the IMA [11]. One prospective study included 100 patients with rectal cancer who underwent anterior sphincter-sparing rectal resection or low anterior rectal resection with high ligation of the IMA and IMV. The results revealed that 63 patients had a lymph node distribution at the root of the IMV and high ligation of the IMV increased the number of lymph nodes dissected [10].

Yuan *et al.* [16] performed an autopsy analysis of 100 adult corpses and divided them into three types according to the traffic branch of the IMV and its sinks. Type I comprises one left colic vein (LCV) and two or three sigmoid veins (SV). According to the confluence of the LCV branches, it is divided into type I1 (the LCV is a single trunk that receives blood from the splenic flexure and descending colon along the way) and type I2 (the upper and lower veins form the LCV, the upper branch holds the blood of the colonic splenic flexure and the upper descending colon, and the lower branch contains the blood of the lower descending colon and the upper sigmoid colon along the way). Type II is composed of two LCVs: the upper branch contains the blood of the splenic flexure of the colon and the upper descending colon, and the lower branch contains the blood of the lower descending colon and the upper sigmoid colon, with one or two SVs flowing directly into the main body. Type III comprises three LCVs, with the upper branch containing the blood of the colonic splenic flexure and the upper descending colon, the middle branch containing the blood of the middle descending colon, and the lower branch containing the blood of the lower descending colon and the upper sigmoid colon, and one or two SVs. There are different positional relationships between the IMV and the left colic artery (LCA): the IMV is located lateral to the LCA; the IMV and LCA cross at the root level of the IMA; the IMV is located on the inside of the LCA and is ≤15 mm away; the IMV is located on the inside of the LCA and is >15 mm away; and the IMV is located on the outside of the LCA and is >50 mm from the root of the IMA [17]. The IMV most commonly drains into the splenic vein, followed by the superior mesenteric vein (SMV). In addition, it may be confluent at the junction of the SMV and splenic vein, the first jejunal vein, and the middle colonic vein [17, 18]. In our study, images of IMV ligation will be collected to facilitate further analysis of the classification/subtypes of the IMV and its potential impact on the findings.

Many European and American professional books recommend high IMV ligation, i.e. ligation and amputation at the lower border of the pancreas, in rectal cancer surgery [19–21]. European and American scholars believe that this method can remove the lymph nodes at the root of the blood vessel and prevent the spread of tumor cells, which is in line with the principle of central vascular ligation. Moreover, this method can increase the freeness of the descending colon and reduce the tension of the anastomosis, which is conducive to intestinal anastomosis. Japanese investigators have reported that there are anatomical lymphatic vessels following the IMV to the pancreas, but the path and intensity of lymphatic drainage have not been determined, and this static lymphatic drainage path does not fully represent the lymphatic drainage path in the clinical sense; thus, ligation and dissection on the tail side of the IMV are recommended to avoid intestinal congestion [22, 23]. Chinese scholars have not yet reached a consensus on the location of IMV ligation and disconnection. The eighth edition of Huangjiasi’s Surgery, a classic surgical textbook in China, suggests that the IMV should be exposed and severed on the outside of the root of the inferior mesenteric artery [4]. Some Chinese scholars have recommended ligation at the root of the IMV, believing that this is in line with the principle of central vascular ligation; others suggest cutting and ligating the IMV at the level of the IMA root [24, 25]. Chinese scholars studied 28 patients who underwent laparoscopic-assisted anterior rectal resection, of whom 12 were ligated with low IMV (ligated and disconnected IMV at the root level of the IMA) and 16 had high IMVs (ligated at the lower edge of the pancreas to dissect the IMV and dissect the lymphoid fat tissue around the IMV). The results revealed that, compared with the IMV at the root-level ligation and dissection of the lower edge of the pancreas, the IMV was similar in terms of surgical indicators (operation time, intraoperative blood loss, postoperative abdominal drainage, postoperative hospital stay), oncological indicators (postoperative pathological stage, total number of lymph nodes, number of positive lymph nodes), and follow-up indicators (postoperative physical score, voiding function score, defecation function score, intestinal function score, and radiotherapy and chemotherapy side effect score), but the postoperative flatus time was shorter (49.30 ± 19.88 vs 67.83 ± 23.00 h, *P *< 0.05) [17]. Previous studies have shown that high ligation and dissection of the IMV can increase the number of lymph nodes obtained and contribute to the lymph node staging of tumors. However, whether this increased lymph node yield translates into a survival advantage remains unclear [26].

The blinding of surgeons and patients is not feasible. However, this approach may introduce bias in postoperative management (e.g. timing of drain removal, discharge criteria) and the assessment of subjective symptoms.

## Conclusions

The optimal level for IMV ligation during radical rectal cancer surgery remains controversial. The IMV anatomy is complex and requires careful intraoperative identification. Current high-level evidence is insufficient to determine whether high ligation improves prognosis compared with low ligation. This multicenter randomized–controlled trial aims to provide robust evidence to guide clinical practice regarding the level of IMV.
